**Figure 4 f4:**
[figure not shown]
Comparison of CARE **(A)** and TARE **(A)** protocols for an exercise session. CARE, Circuit Aerobic and Resistance Exercise; TARE, Traditional Aerobic and Resistance Exercise; HRmax, maximum heart rate; 1RM, 1 repetition-maximum.

#### 2.4.1 Circuit Aerobic and Resistance Exercise (CARE)

The CARE intervention is a systematically progressed AE and RE program. The intensity of exercise begins at a low intensity and gradually increases to high intensity over the 4-month mesocycles to optimally elicit improvements in body composition, physical function, and cardiometabolic makers (25). The details of the linear periodization for the CARE program are described in **Table 2**. In brief, the first mesocycle, the preparatory period, is performed at moderate intensity (60-65%) to increase tolerance of higher training intensities that occur later in the program (26). The majority of the program (weeks 5-12, mesocycles 2-3) are performed at moderate-to-vigorous intensity (67-80%) to emphasize increases in lean mass (27) and decreases in fat mass (28), with a hypertrophy training goal during RE (26), and intensities approaching 80% VO_2peak_ during AE (28). The fourth mesocycle incorporates higher intensities (80-85%), which are necessary to further obtain improvements as performance increases (29). The volumes of the RE decrease throughout the intervention period to accommodate the increase in intensity, while the volumes of the AE increase to match the volumes performed in the other exercise group. AE is performed on a treadmill or a bike, and RE consists of 6 exercises, including leg press, chest press, leg curl, seated row, leg extension, and shoulder press (lateral raise or scaption will be substituted if participants are unable to press overhead), using exercise machines and dumbbells. Each upper- and lower-body exercise is performed in an alternating manner to provide active recovery periods for the exercised muscle groups between each exercise and to constitute circuit-style training. Specifically, participants begin with AE, then alternate 3 lower-extremity and 3 upper-extremity REs that target major muscle groups with no rest between RE exercises. After completion of a set of exercises in one circuit, participants return to AE to start the next set after 1-minute rest between sets, until all prescribed sets are completed.

**Table 2 T2:** Periodization model for exercises in the CARE program.

Training Period	Resistance Exercise		Aerobic Exercise	
	Intensity (%1RM)	Volume (repetitions x sets)	Intensity (%HR_max_)	Volume (duration x sets)
**Mesocycle 1** **(Preparatory)**				
Weeks 1-2	60%	15 x 3	60%	5 min x 3
Weeks 3-4	65%	12-15 x 3	65%	5 min x 3
**Mesocycle 2** **(Moderate Intensity)**				
Weeks 5-6	70%	10-12 x 3	70%	5 min x 4
Weeks 7-8	70-67%	10-12 x 3	75%	5 min x 4
**Mesocycle 3** **(Vigorous Intensity)**				
Weeks 9-10	70%	10 x 3	80%	5 min x 5
Weeks 11-12	75%	8-10 x 3	80%	5 min x 5
**Mesocycle 4** **(High Intensity)**				
Weeks 13-14	80%	8 x 3	85%	6 min x 5
Weeks 15-16	85%	8 x 3	85%	6 min x 5

RM, repetition maximum; x, times (e.g., 8 x 3 = 8 repetitions completed three times); HR_max_, maximum heart rate; min, minutes.

#### 2.4.2 Traditional Aerobic and Resistance Exercise (TARE)

Patients assigned to the TARE group begin training sessions with AE on the treadmill or bike, followed by a total body RE with the same 6 exercises as in the CARE intervention. The duration and intensity of AE are progressing from 15 to 30 minutes and from 65 to 80% of HR_max_, respectively. The initial RE will be 60% 1RM and will increase by 10% when a participant is able to complete three sets of 10 repetitions in two consecutive sessions. Each session consists of AE and 3 sets of each RE with a 45-second rest period are taken between each RE set, which takes approximately a total of 80 minutes. Both the AE and RE are matched in volume to that of the CARE program.

#### 2.4.3 Attention-Control (AC)

Patients randomized to the AC group complete a 16-week home-based stretching program with the same stretches in the CARE and TARE groups at the end of their sessions. Minimal caloric expenditure is expected to be incurred as the stretches are low-intensity, low-impact, and low-volume. Participants are given an instructional booklet and trained in how to use the booklet to maximize the standardization of the home-based stretching (30) and increase compliance (31). Participants are also asked to complete weekly records detailing flexibility compliance and any physical activity performed outside of the study. At the end of the initial 16-week period, the AC group will be offered the 16-week CARE program weeks. Participants in the AC group who choose to perform the CARE program will complete one more assessment after the exercise program. Those who do not choose to partake in the CARE program will be finished with the study after the initial 16-week period.

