#### 2.5.4 Exploratory Outcomes

##### 2.5.4.1 Breast Cancer Outcomes

Breast cancer events are commonly used in lifestyle trials (71–75). Disease-free survival (DFS) is defined as the time from randomization to the documentation of the first of any of the following events: invasive ipsilateral breast tumor recurrence; local, regional, distant recurrence; invasive contralateral breast cancer; or ipsilateral and contralateral ductal carcinoma in situ, second primary invasive cancer (excluding carcinoma *in situ* and skin cancer other than melanoma). Overall survival (OS), distant DFS (DDFS), and recurrence-free interval (RFI) are included as exploratory endpoints. OS is defined as the time from randomization to death from any cause. DDFS is defined as events that are either lethal (death from any cause) or a direct threat to patient survival (distant recurrence or second primary invasive cancer). RFI is defined as events directly attributable to the original breast cancer including invasive ipsilateral breast tumor recurrence; local, regional, or distant recurrence; and death from breast cancer. These efficacy end points are assessed by reviewing medical records annually for 8 years from the time the participant enrolls in the study. Participants are called by phone to confirm their disease status or to assess their disease status if their medical records are unavailable.

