### 2.6 Follow-Up Assessments

After the 16-week intervention, participants in the TARE and CARE groups will return 4 and 8 months after the post-intervention assessments to repeat the outcome measure testing. Medical record abstraction will occur for 8 years thereafter to assess prognostic outcomes (i.e. OS, DFS, etc.). During the follow-up period, participants will be encouraged to exercise independently, without study team supervision/intervention.

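### The plan conflicts on whether attention-control women who decline CARE stay in event follow-up after week 16, and on when the 8-year follow-up starts

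*Protocol article*

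**What the plan says.** Three sections of the protocol article bear on this.

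- **Section 2.4.3 (Attention-Control)** offers AC women the CARE program after their 16 weeks. Of those who accept it says: "Participants in the AC group who choose to perform the CARE program will complete one more assessment after the exercise program". Of those who do not: "Those who do not choose to partake in the CARE program will be finished with the study after the initial 16-week period".
- **Section 2.5.4.1 (Breast Cancer Outcomes)** defines DFS, OS, DDFS and RFI. DFS and OS run from randomisation. The endpoints are "assessed by reviewing medical records annually for 8 years from the time the participant enrolls in the study", with a second source: "Participants are called by phone to confirm their disease status or to assess their disease status if their medical records are unavailable". No arm is excluded.
- **Section 2.6 (Follow-Up Assessments)** first says that "participants in the TARE and CARE groups will return 4 and 8 months after the post-intervention assessments to repeat the outcome measure testing". It then says: "Medical record abstraction will occur for 8 years thereafter to assess prognostic outcomes".

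A footnote to Figure 3 also concerns AC decliners. It says only that they skip selected testing at one time point, which is weaker than leaving the study.

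**The concern.** Two things do not fit together.

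**Who is followed.** A woman who has left the study at week 16 cannot also be under annual record review and telephone contact for 8 years. The first annual review would come well after she had left.

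**From when.** The 8 years start at enrolment in one section and after the intervention, or after the follow-up visits, in another. DFS and OS have a further origin, randomisation, which follows the baseline assessments.

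The first point matters more. If section 2.4.3 is applied literally, whether an AC woman is followed for recurrence and death depends on her own decision, made after randomisation, about taking up CARE. That decision may be related to prognosis. Censoring decliners at week 16 would then not be safely non-informative, and the AC arm would no longer be the group that was randomised. The article's Discussion lists breast cancer events among the outcomes on which CARE is to be evaluated, so comparisons between arms are intended, although as exploratory ones.

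**Working it through.** **The trial's own numbers.** Section 2.8 uses an effect size of 0.5, two-sided alpha 0.025 and 80% power. The two-sample t-test solution is 77.31, so 78 per group. With 15% dropout, 78 / 0.85 = 91.8, so 92 per group, and 3 × 92 = 276. These figures reproduce and do not depend on the point at issue. No event count or power is stated for the long-term endpoints.

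**When follow-up ends, in years from enrolment.** For this purpose enrolment and the start of the 16 weeks are treated as the same day.

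| Rule | Calculation | End of event follow-up |
|---|---|---|
| Section 2.5.4.1 | 8 | 8.00 |
| Section 2.6, counted from the end of the intervention | 16/52.18 + 8 = 0.31 + 8 | 8.31 |
| Section 2.6, counted from the 8-month visit | 0.31 + 8/12 + 8 | 8.97 |
| Section 2.4.3, decliner, literal reading | 16/52.18 | 0.31 |

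The two clocks therefore differ by 0.31 to 0.97 years.

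**Planned person-years under the literal reading.** Let d be the share of AC women who decline. The documents give no value, so d is assumed over a range. Acceptors are taken to be followed for the full 8 years, and deaths and losses are ignored.

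AC person-years = 92 × [(1 − d) × 8 + d × 0.31]. Each exercise arm has 92 × 8 = 736.

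| d (assumed) | AC person-years | Ratio to one exercise arm |
|---|---|---|
| 0% | 736 | 1.00 |
| 25% | 559 | 0.76 |
| 50% | 382 | 0.52 |
| 75% | 205 | 0.28 |

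If section 2.5.4.1 applies to everyone, the ratio is 1.00 whatever d is.

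**What the selected-follow-up scenario requires.** It needs section 2.4.3 to govern decliners and section 2.5.4.1 to govern acceptors. Section 2.4.3 promises acceptors only one more assessment and does not mention the 8 years for them. A literal reader can reach this combination, because only decliners are said to be finished, but no section spells it out.

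**The case against.** The strongest reply is that no section removes any AC woman from event follow-up. Section 2.5.4.1 governs these endpoints, is not restricted by arm, and relies on records and telephone, which need no study visit. Section 2.4.3 describes the intervention, and the sentence before the disputed one is about an extra assessment, so finishing may mean only the program and on-site testing. The Figure 3 footnote supports that. This stands: unequal follow-up is a risk under one reading, not something the plan prescribes.

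Three stronger inferences are tempting, and the documents do not support them.

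- *Events are followed unequally by arm because there are two clocks.* In section 2.6 only the sentence on repeat testing names TARE and CARE; the sentence on record abstraction names no arm. A difference arises only if the later clock is applied to the exercise arms and the enrolment clock to AC. The ratio would then be 736 / (92 × 8.97) = 736/826 = 0.89, but no section says to do this. Differing administrative censoring times are in any case not in themselves a bias in a time-to-event analysis.
- *Fitter women would choose CARE, so a benefit would be hidden.* The direction of any selection is not given and cannot be derived.
- *A known share of the AC arm would be lost.* Every decline rate used here is an assumption.

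It is also fair to say that offering CARE to AC women at week 16 already complicates any 8-year contrast with AC, however this wording is settled. And a condensed article may leave the mechanics of long-term follow-up to the full protocol. That would excuse missing detail. It does not excuse printed rules that conflict.

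**Conclusion.** The point holds as an internal conflict that must be reconciled. Section 2.4.3 is at odds on its face with section 2.5.4.1 on whether AC decliners stay in event follow-up, and sections 2.5.4.1 and 2.6 disagree on the start of the 8 years by about 0.3 to 1.0 year.

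The consequence is conditional. Under the literal reading, with acceptors followed in full, AC follow-up would fall to between about three quarters and one quarter of that in an exercise arm for assumed decline rates of 25% to 75%, and it would be selected by a post-randomisation choice. Under the benign reading nothing is lost.

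The reach is limited to the exploratory long-term comparisons with AC. The primary analysis uses the 2- and 4-month data and is unaffected, as are the sample size and, as far as section 2.4.3 goes, CARE versus TARE. The conflict is still worth correcting while the trial runs, because women released at month 4 may be hard to reach again years later.

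**What to change.** 1. In section 2.4.3, state that AC women who decline CARE finish the intervention and study visits at 16 weeks but remain in the annual record review and telephone confirmation of disease status.
2. In sections 2.5.4.1 and 2.6, state one 8-year clock for all 276 randomised women, counted from randomisation, which is already the origin of DFS and OS.

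The cost is wording in three sections, plus record review and telephone contact for AC decliners, which section 2.5.4.1 already plans. The consent text should be checked to confirm that it covers continued follow-up of women who have finished study visits.

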### 2.5 Outcome Measures

The outcomes are assessed at baseline, mid-intervention, and post-intervention with 4- and 8-month follow-up periods. All measures are performed by trained study personnel at the Dana-Farber Cancer Institute.

#### 2.5.1 Primary Outcomes

##### 2.5.1.1 Adipose Tissue Chronic Inflammation

M1 and M2 phenotypes are the primary outcomes. As the M1/M2 system alone does not accurately represent the heterogeneity of adipose tissue macrophages (ATMs) in obesity (32), we also examine secretion levels of inflammatory cytokines to provide a comprehensive examination of the presence of chronic adipose tissue inflammation, which include interleukin (IL)-6, IL-8, tumor necrosis factor-α (TNF-α), high-sensitive c-reactive protein (hs-CRP), leptin, and adiponectin. Participants can volunteer to undergo an abdominal subcutaneous fat biopsy under local anesthesia performed by a certified physician assistant ([name]) and are asked to refrain from foods for 12 hours and anti-inflammatory pharmaceuticals for 3-5 days prior to biopsy. Participants lie supine on the examining table while the biopsy site is prepped and draped in a sterile fashion. Under ultrasound guidance performed by a licensed technician, a local anesthetic is injected into subcutaneous abdominal fat (midway between the iliac crest and umbilicus) after which a small skin nick is made. The core biopsy device equipped with a 13-gauge needle is inserted at the incision site.

Approximately 4 samples are taken from a single site, roughly a total of 40mg to 120mg of fat tissue. The biopsy is taken at the Brigham and Women’s Hospital and transported to the Immune Assessment Laboratory at the Center for Immuno-Oncology for processing. One sample is flash-frozen in liquid nitrogen and stored until RNA isolation, and the rest of the tissue is digested with a collagenase solution to create a single-cell suspension. Appropriate batch testing is conducted by research staff blinded to randomization.

##### 2.5.1.2 Systemic Inflammation

Fasting blood is taken from the antecubital vein by a trained phlebotomist following the biopsy procedure. For each sample, two 10 ml tubes are collected into EDTA and Serum tubes, along with one additional lavender topped tube (whole blood in EDTA). Samples are centrifuged and then aliquoted and stored at -80°C for future measures. Blood samples are then transported to the Brigham Research Assay Core for batch analyses for IL-6, IL-8, TNF-a, and hs-CRP. Other related systemic biomarkers such as leptin, adiponectin, insulin resistance, insulin-like growth factor (IGF)-1, IGF binding protein (IGFBP)-3, lipid profile, estradiol, sex hormone-binding globulin (SHBG), and free testosterone are also analyzed through commercially available blood testing kits.

#### 2.5.2 Secondary Outcomes

##### 2.5.2.1 Sarcopenic Obesity and Body Composition

Sarcopenic obesity is determined by body composition measured by dual-energy X-ray absorptiometry (DXA; *Hologic Inc., Marlborough, MA*). Appendicular fat-free mass (AFFM) is measured from a whole-body, hip, and spine scan, and predicted AFFM is calculated using the following equation: -14,529 + (17,989 * height in meter) + (0.1307 * total fat mass in kilograms) (33). A residual value of ≤-3.4 is defined as an individual having sarcopenic obesity (33). Lean mass, fat mass, and body fat % are also obtained from the whole-body DXA scan. A constant-tension tape measure is used to obtain waist circumference, defined as the distance around the waist using the umbilicus as the reference point, and hip circumference, defined as the distance around the widest girth of the buttocks using the greater trochanter as a landmark. Body composition is also assessed *via* bioelectrical impedance using a validated device (*Tanita 780, Arlington Heights, IL*) (34). The device estimates body fat using an algorithm based on their age, sex, height, and body weight.

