**Methods:**

The AIM trial is a prospective, three-armed, phase II randomized controlled trial investigating the effects of a 16-week supervised circuit aerobic and resistance exercise (CARE) program versus a traditional aerobic and resistance exercise (TARE) program and attention control (AC) on adipose tissue inflammation in breast cancer survivors. 276 patients who are diagnosed with stage 0-III breast cancer, post-treatment, sedentary, and centrally obese are randomized to one of the three groups. The CARE and TARE groups participate in thrice-weekly supervised exercise sessions for 16 weeks. The AC group are offered the CARE program after the intervention period. The primary endpoint is adipose tissue inflammation assessed by core biopsy and blood draw. The secondary and tertiary endpoints are sarcopenic obesity, physical fitness and function, and patient reported outcomes. The exploratory outcomes are long-term breast cancer outcomes.

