### 2.8 Sample Size

We anticipate recruiting 276 patients over a 48-month period and randomizing 92 patients to each arm of the study. Our hypotheses and analyses regarding our primary and secondary outcomes will reflect the comparison between CARE vs. TARE, and CARE vs. AC. Since the primary analysis involves two statistical comparisons, we will apply Bonferroni adjustment to control the overall type I error rate at 0.05 level. We estimated samples sizes for these two comparisons with each evaluated at two-sided alpha = 0.025. Our estimates of exercise intervention effect sizes were derived from randomized clinical trials (78–80) in addition to our preliminary data (81); most significantly, a study comparison of traditional endurance training vs. high-intensity circuit training (80) with effect sizes for outcomes common to our proposed trial (fat mass, lean body mass) was approximately 0.5-0.6. Effect sizes comparing exercise interventions to AC groups were larger, on 0.7-1.0. Our preliminary data compared exercise to AC (15 subjects per group), effect sizes were on the order of 1.0 (body composition measures) to 2.5-3.0 (inflammatory and other biomarkers) (81). The sample size determination was based on the comparison of the primary outcome between the CARE and TARE group because we expected that the difference between the CARE and AC group was larger than that between the CARE and TARE groups. We used an effect size of 0.5, two-sided alpha=0.025, and 80% power to estimate the sample size for comparisons of CARE vs. TARE, yielding a required 78 participants per group. To account for an anticipated 15% dropout rate, we will randomly assign 92 participants to each of the three groups. This will provide 80% or higher power to detect effect sizes of 0.5 and higher for other outcomes. For the optional biopsies, the sample size has been estimated at 50 participants per group based on our preliminary work (81). This will provide 80% power to detect a between-group difference, at a two-sided 0.025 alpha level, when the effect size is 0.9 for biopsy outcomes.

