### 2.9 Statistical Analysis

Initial descriptive analyses will be used to evaluate baseline comparability among the three intervention groups, using ANOVA, or Kruskal-Wallis tests for continuous variables and chi-square tests for categorical variables. Unless otherwise specified, Statistical testing will be conducted at a two-sided 0.05 alpha level to determine statistical significance. For our primary and secondary outcomes, the variables used for the primary analysis will be the 2- and 4-month measurements of trial outcomes assessed during and at the end of the intervention period. Linear mixed-effects models will be used with the longitudinal data for the between-group comparisons, where two indicator variables for the treatment group (TARE, AC) relative to CARE, the baseline value of the outcome, and an indicator variable for measurement time (2-month/4-month) will be included as fixed-effects and subjects as random-effects in the models. With Bonferroni correction applied, the Wald test will be performed at 0.025 two-sided alpha level for each of the two comparisons regarding treatment effects (i.e., CARE vs. TARE, and CARE vs. AC); the between-group differences will be reported with corresponding 0.975 two-sided confidence intervals. Significant group differences will be followed by stratified analyses within measurement time (two and four months), and testing of group-time interactions, to evaluate treatment group differences within measurement time.

Post-intervention outcomes will be evaluated using the same linear mixed-effects models. The dependent variables will be the 8- and 12-month post-intervention measures, with the 4-month post-intervention measure, included as a fixed-effect.

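### The printed equation for predicted appendicular fat-free mass, which defines sarcopenic obesity, mixes gram-scale and kilogram-scale terms and cannot be applied as written

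*Protocol article*

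**What the plan says.** The abstract lists sarcopenic obesity among the trial's endpoints: "The secondary and tertiary endpoints are sarcopenic obesity, physical fitness and function, and patient reported outcomes". Section 2.5.2 places it under secondary outcomes.

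Section 2.5.2.1 contains the whole definition. Measured AFFM comes from DXA: "Appendicular fat-free mass (AFFM) is measured from a whole-body, hip, and spine scan". No unit is given for it. Predicted AFFM is printed, after a leading minus sign, as "14,529 + (17,989 * height in meter) + (0.1307 * total fat mass in kilograms", and the classification rule is: "A residual value of ≤-3.4 is defined as an individual having sarcopenic obesity". The cut-off also carries no unit, and the residual is not spelled out as measured minus predicted. Both the equation and the cut-off are attributed to reference 33.

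Section 2.9 states the analysis: "For our primary and secondary outcomes, the variables used for the primary analysis will be the 2- and 4-month measurements of trial outcomes". It continues: "Linear mixed-effects models will be used with the longitudinal data for the between-group comparisons", with the baseline value as a covariate, a Wald test, and "the between-group differences will be reported with corresponding 0.975 two-sided confidence intervals". No separate model is named for a yes/no outcome.

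**The concern.** Within one definition, two coefficients carry a comma (14,529 and 17,989) while the third coefficient and the cut-off carry a decimal point (0.1307 and 3.4). Elsewhere the article also uses the point for decimals, for example 25.0 kg/m² in the Introduction and 91.4 cm in section 2.5.3.6. The natural reading of the commas is therefore as thousands separators. That puts the first two terms on a gram scale and leaves the fat term and cut-off on a kilogram scale.

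This is the only definition of a named secondary outcome in the document. Anyone who programs or replicates the outcome from it gets either a variable with no variation or one from which fat mass has all but disappeared. The fat term is what sets the AFFM expected of a woman according to her adiposity. Without it the rule is, in effect, a height-adjusted threshold for low lean mass.

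A smaller question follows from section 2.9. The outcome is defined as a yes/no status, but all secondary outcomes are sent to a linear mixed model.

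**Working it through.** **Plan's own figure.** The article prints no predicted AFFM and no prevalence, so there is nothing to reproduce. The check evaluates the equation under each possible reading.

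**Inputs from section 2.5.2.1:** intercept, height coefficient, fat coefficient (fat mass in kg), cut-off -3.4.

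**Assumed, not in the article:** height 1.60 m and fat mass 38 kg for the worked example; height 1.45 to 1.80 m, fat mass 20 to 60 kg and AFFM 12 to 28 kg for the range; residual = measured minus predicted.

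**Reading A: commas as thousands, AFFM in kg.**
- Predicted = -14,529 + 17,989 × 1.60 + 0.1307 × 38 = -14,529 + 28,782.4 + 4.97 = 14,258.4.
- Over the assumed range, residuals run from about -11,530 to -17,847. All lie below -3.4, so 100% are cases.

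**Reading B: commas as thousands, AFFM and cut-off both in grams.**
- The prediction is again 14,258.4, now in grams. The fat term is 4.97 g, or 4.97 / 14,258.4 = 0.03% of it.
- Case threshold = 14,258.4 - 3.4 = 14,255 g, about 14.3 kg.

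**Reading C: commas as decimal points, everything in kg.**
- Predicted = -14.529 + 17.989 × 1.60 + 0.1307 × 38 = -14.529 + 28.782 + 4.967 = 19.22 kg. The fat term is 4.97 / 19.22 = 26% of it.
- Case threshold = 19.22 - 3.4 = 15.82 kg.
- Over the assumed range the prediction is 14.2 to 25.7 kg, a scale on which -3.4 kg can discriminate.

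**B against C.** The threshold differs by 15.82 - 14.26 = about 1.6 kg. Reading B drops almost 5 kg of prediction, but it also shrinks the cut-off from 3.4 kg to 3.4 g, and the two partly cancel. In kg, the difference (C minus B) is (0.1307 - 0.0001307) × fat mass - (3.4 - 0.0034). It is zero at 3.3966 / 0.13057 = 26.0 kg of fat. Above that, B misses cases; below it, B adds some (at 1.60 m and 20 kg of fat the thresholds are 14.25 kg under B and 13.47 kg under C).

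**Illustration of prevalence.** This is a simulation with assumed inputs: height mean 1.62 m, SD 0.065; fat mass mean 38 kg, SD 9; AFFM scattered around Reading C.

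| Residual SD (kg) | A | B | C |
|---|---|---|---|
| 2 | 100% | 1.5% | 4.4% |
| 2.5 | 100% | 3.6% | 8.7% |
| 3 | 100% | 6.0% | 12.7% |

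**Model.** Section 2.5.2.1 defines a status. Section 2.9 puts secondary outcomes into a linear mixed model and reports between-group differences. On a 0/1 variable that is a linear probability model. The planning effect size in section 2.8 ("We used an effect size of 0.5, two-sided alpha=0.025, and 80% power to estimate the sample size for comparisons of CARE vs. TARE") is a standardised mean difference and does not transfer directly to a proportion.

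**The case against.** The strongest reply is that this is a printing slip. Replacing two commas by points gives an equation that works in kilograms and fits the cut-off, and the article cites a source for both. A predicted limb mass of 14,000 kg would hardly survive a first look at the derived data. This stands as an account of the likely cause, and it limits what may be inferred. It does not remove the error from the only definition printed.

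A reader might go further and infer that the trial will classify every woman as a case, or that prevalence moves from 100% to almost none and no group difference could be detected either way. The article does not support this. The 100% figure requires AFFM in kilograms. In a literal grams reading the threshold moves by about 1.6 kg in the worked example, which gives too few cases but not almost none. To approach almost none, one must take the first two terms as grams, leave the fat term unconverted and yet convert the cut-off to kilograms (14,258 - 3,400 = 10,858 g, about 10.9 kg). Loss of any detectable difference follows only where everyone is a case.

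On the model, it is fair to answer that section 2.5.2.1 also lists lean mass, fat mass and body fat percentage, which suit a linear mixed model and retain the continuous information. The article never says that the 0/1 status is the dependent variable, and the fuller plan may settle it. That makes the model question secondary. Still, section 2.9 as written covers all secondary outcomes without exception.

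**Conclusion.** The equation is wrong as written. No single unit for AFFM reconciles the intercept, the height coefficient, the kilogram-based fat term and the cut-off of -3.4. This follows from the printed text alone.

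The size of the consequence depends on the reading. With AFFM in kilograms, all women are cases. With AFFM and cut-off in grams, the fat contribution shrinks a thousandfold and the case threshold is about 14.3 instead of 15.8 kg at an assumed 1.60 m and 38 kg of fat. Cases are then under-counted wherever fat mass exceeds about 26 kg, which is likely, though not stated, for most of a centrally obese population. The prevalence figures are illustrative and rest on the assumed distributions.

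That the commas stand for decimal points is an inference from the scale of the result, since the cited source was not available for checking. A reader might also conclude that the trial's derivation is faulty; the article gives no evidence of that. The mismatch between a yes/no definition and a linear model is a lesser point that calls for clarification.

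**What to change.** 1. Check the equation and cut-off against the cited source and print them in one set of units. If the decimal-point reading is confirmed: predicted AFFM (kg) = -14.529 + 17.989 × height (m) + 0.1307 × fat mass (kg).
2. State that the residual is measured minus predicted AFFM in kg, and that the cut-off is -3.4 kg.
3. Verify the derivation code on a few records by hand. Predictions should fall in the range of roughly 14 to 26 kg for women within the heights and fat masses assumed above.
4. State which form of the outcome is modelled. Enter the continuous residual in the linear mixed model of section 2.9. If the yes/no status is also analysed, use a logistic mixed model or GEE for it.

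The cost is a correction of wording and a check of the code. No new data and no change to the sample size are needed.
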